**Fig. 2 Fig2:**
[figure not shown]
Logic model for evaluation of Responsive CARE intervention

### Procedures

Eligible child and caregiver participants who attend during the study period will be approached by a research assistant at their outpatient burn clinic appointment and informed of the study and invited to participate in quantitative data collection (see Fig. 3). Data will be collected using iPads (or pencil and paper if preferred by the participant) in the outpatient clinic setting. Interviews will be completed with caregivers on-site at the recruiting centre or via the telephone (if preferred) when convenient for the participant. Interviews will be audio-recorded and transcribed verbatim.

**Fig. 3 Fig3:**
[figure not shown]
Flow diagram of enrolment in feasibility study

Health professional participants who attend an existing weekly educational clinical meeting at the recruiting centre during week 1 (of the 1-month training period between the control and intervention period) will be invited to complete the Responsive CARE intervention. In week 1, a 10-min educational demonstration (Additional File 4) of how to access the web-based intervention, as well as an overview of the content will be delivered in a burn educational meeting by champions (MS, RK). Personal log-in details for health professionals (that are not connected to staff records) will be provided following informed consent regarding details for accessing the web-based intervention (Additional File 5). Staff are able to access the intervention from any web-based platform of their choosing. The training will be repeated weekly (if desired by the clinical team) or individually upon request throughout the 1-month training period. Educational demonstrations in week 3 will also include an interactive whiteboard video (6 min) on responsive trauma-informed CARE and a 7 min interactive whiteboard video on self-CARE in week 4. Researchers will record the allocated log-in details so they are available upon request by any user. Verbal reminders of the invitation to participate will be repeated at the weekly educational clinical meeting throughout the 1-month period. Health professionals will be able to access the intervention using their personal log-in until completion of the intervention period follow-up data collection (i.e. 6-months post-baseline). Upon commencing the responsive CARE intervention, health professionals will complete a survey to consent (or not) to research and complete demographic details such as their profession, gender, age, years of experience with hospital-based care, years in current burns role and previous training in trauma-informed care (see Additional File 6).

All health professionals working within the burn clinical team at the time of recruitment will be informed at the weekly educational clinical team meeting or approached individually by a researcher and invited to participate in a 1:1 interview or focus group on-site at the recruiting centre. Senior managers will be approached individually by a senior researcher and invited to participate in a 1:1 interview. Interviews and focus groups will be audio-recorded and transcribed verbatim. Transcripts will be returned to health professionals for member checking.

### Implementation plan

The Consolidated Framework for Implementation Research (CFIR) [38] will be used to guide evaluation of the factors influencing implementation identified through qualitative interviews and technical assistance logs, knowing these factors will improve understanding of the barriers and enablers to implementation of the intervention as planned and proposed. The CFIR (a widely cited and rigorously developed determinants framework for implementation) consists of five domains, with each domain consisting of a number of constructs identified in the literature as impacting successful implementation. These findings will be analysed and actioned to inform adaptations and future implementation blueprint.

### Outcomes

#### Feasibility outcomes

Acceptability (level of satisfaction, intention to continue use and perceived appropriateness of the intervention) and practicality (perceived sustainability within existing infrastructure) of the intervention, as well as factors affecting implementation will be explored through the qualitative interviews with staff carried out throughout the study period. Actual use (versus expressed interest or intent to use) will be observed via ilearn digital records to assess demand for the intervention. Signs of distress on patient-centred outcome measures (see below) during the control period will also be used to assess the need for trauma-informed care. An attrition diagram will be developed demonstrating usage, dose and engagement. Implementation outcomes will explore the perceived impact of the responsive CARE intervention on clinician behaviours (for example, use of validated screening tools, empathic communication strategies) according to quantitative and qualitative data collected from staff and caregivers, as well as barriers and enablers in the implementation environment. Changes required to support the uptake of the Responsive CARE intervention in the training and intervention period will be recorded in technical assistance logs in which the ongoing consultation process, any top-up training and alterations to processes will be recorded using narrative description.

### Primary patient-centred outcomes

The primary outcome measures of effectiveness to be tested for the main study are pain (self-report or behavioural observation), itch and distress. The Face, Legs, Arms, Cry, Consolability (FLACC) pain scale [39, 40] will be completed by health professionals as a behavioural measure of pain severity. An 11-point numeric rating scale (NRS) will be used by parents and children 8 years or older to rate pain and itch intensity [41]. The NRS is scored from zero to ten, with zero equal to “no pain or itch” and ten equal to “unbearable pain or itch”. Distress will be measured using the Paediatric Emotional Distress Scale—Early Screener [40, 42] for children below 6 years and the Child Traumatic Stress Questionnaire [43] for children aged 7 years and above.

Patient-centred outcome measures to be collected at baseline, 3-months and 6-months post-baseline are summarised in Table 2.

**Table 2 Tab2:** Patient-centred outcome measures and timepoints when administered

Area of focus	Completed by			Outcome measure	Study period (control and intervention)		
	HP	C	YP		Baseline	3-months	6-months
Pain and itch (primary outcome)	X			The Face, Legs, Arms, Cry, Consolability (FLACC) [39, 40]	X	X	
		X	X	Numeric Rating Scale [41]	X	X	
Distress (primary outcome)		X		Pediatric Emotional Distress Scale – Early Screener^a^ [42]	X	X	X
			X	Child Traumatic Stress Questionnaire^b^ [43]	X	X	X
Stress		X		Perceived Stress Scale [44]	X	X	X
Satisfaction with treatment		X	X	Numeric Rating Scale (0 to 10)	X	X	X
Health-related quality of life		X	X	Brisbane Burn Scar Impact Profile [45–47]		X	X
		X	X	EuroQol-5D-Y^c^ [48, 49]	X	X	X
		X	X	CHU-9D^d^ [49, 50]	X	X	X

*HP* health professional, *C* caregiver, *YP* young person aged over 8 years (unless otherwise indicated)

^a^ For children below 6 years

^b^ For children aged 7 years and older ^c^ Administered to caregivers of children 3 years and older  ^d^Administered to caregivers of children 2 years and older

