### Participants

#### Inclusion criteria

All children and caregivers attending an outpatient service for change of burn wound dressing or burn scar management during the control or intervention period will be eligible to participate. Health professional participants (e.g. medical staff, occupational therapists, nursing staff, social workers, senior managers) will be those involved in the management of children with burns during the study period. Students who are members of the treating burn team for less than 2 weeks during the study will be excluded.

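### Six-year-olds are eligible, but the plan lists no instrument for the primary outcome distress at that age

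*Protocol article*

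**What the plan says.** Under Primary patient-centred outcomes, the Protocol article states: "The primary outcome measures of effectiveness to be tested for the main study are pain (self-report or behavioural observation), itch and distress". Two instruments are listed for distress. The Paediatric Emotional Distress Scale – Early Screener is "for children below 6 years", and the Child Traumatic Stress Questionnaire takes over one year later; the full rule reads "for children below 6 years and the Child Traumatic Stress Questionnaire [43] for children aged 7 years and above". Footnote a of Table 2 repeats the first limit, and footnote b gives the second as "For children aged 7 years and older". Both instruments are scheduled at baseline, 3 months and 6 months.

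Eligibility has no matching gap. The Inclusion criteria admit "All children and caregivers attending an outpatient service for change of burn wound dressing or burn scar management during the control or intervention period", the Exclusion criteria name no age, and Study setting gives the clinic's range as 0–18 years.

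Under Data analysis, Patient-centred outcomes, the results are to be stratified by age so that the strata follow the versions of the measures. Models adjust for baseline values where appropriate, and child traumatic stress symptoms are among the potential confounders named in advance.

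**The concern.** A child who has turned 6 but not 7 can be enrolled, yet the plan gives no distress measure for that child. The gap is fixed by the plan's own age limits, so it is not ordinary missing data. The planned sensitivity analysis imputes values lost over follow-up under a missing-at-random assumption. It is not built for children who were never assigned an instrument, and no score at that age exists from which to learn.

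Three uses of the distress data are touched:

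- The age-stratified comparison has no stratum for age 6, so these children would drop out of it without comment.
- Child traumatic stress may serve as a covariate. If it is taken from these two instruments and adjusted for, six-year-olds could also drop out of adjusted models for other outcomes.
- Feasibility outcomes uses signs of distress in the control period to judge the need for trauma-informed care. That judgement would rest on the other ages only.

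**Working it through.** **Inputs.** Anticipated sample: 180 children, from 30 new referrals a month (Recruitment, Quantitative study component) over a 3-month control and a 3-month intervention period (Study design). Age range: 0–18 years (Study setting). Instrument limits: under 6, and 7 or over (text and Table 2 footnotes a and b). Visits: baseline, 3 and 6 months (Table 2).

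**Step 1: the plan's own figure.** 30 × (3 + 3) = 180. It is reproduced.

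**Step 2: which ages are uncovered.** Take ages 0–18 in completed years, remove those below 6, then remove those of 7 and above. What remains is age 6 only, that is 6.0 to under 7.0 years. Text and footnotes agree, so this is not a slip in one of two places. Nothing else fills the gap: the Perceived Stress Scale is a separate row of Table 2, headed Stress and completed by caregivers. The table's default age for young-person report is overridden by footnote b for the Questionnaire.

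**Step 3: how many children at baseline.** The documents give no age distribution, so this step rests on an assumption.

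| Assumed share aged 6 | Of 180 | Per period (of 90, if split evenly) |
|---|---|---|
| 2% | 3.6 | 1.8 |
| 1/18 = 5.6% (uniform ages) | 10.0 | 5.0 |
| 10% | 18.0 | 9.0 |

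**Step 4: how many visits are lost.** The plan does not say whether age at baseline or age at each visit decides the instrument. With uniform ages over 18 years:

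- *Age at baseline decides.* Everyone aged 6.0 to under 7.0 at baseline misses all three visits: 1.0/18 × 180 = 10 children.
- *Age at each visit decides.* To miss all three, a child must be 6.0 or older at baseline and still under 7.0 six months later, so 6.0 to under 6.5 at baseline: 0.5/18 × 180 = 5 children (2.8%). To miss at least one, a child must be 5.5 to under 7.0 at baseline: 1.5/18 × 180 = 15 children (8.3%).

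Under the second rule, a child aged 5.5 to under 6.0 at baseline has a baseline score but enters the gap during follow-up. A child aged 6.5 to under 7.0 at baseline has a score by 6 months but no baseline value to adjust for.

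**The case against.** The case for leaving this alone has several parts.

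**Other primary outcomes are intact.** This stands. A six-year-old still has FLACC from the health professional and the caregiver's numeric ratings of pain and itch. One of three primary outcomes is lost, not the child's primary data.

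**No bias between periods is shown.** This stands too. A reader might infer that the gap distorts the comparison of control with intervention. The same age rule applies in both periods, and the under-6 and 7-and-over data are analysed in separate strata anyway, so leaving out age 6 does not by itself shift either comparison.

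**The loss is not necessarily complete.** A reader might infer that every six-year-old lacks distress at all three visits. The documents do not support this as a general statement, because it needs the age-at-baseline rule, which is not stated.

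**It may be loose wording.** The article handles this boundary loosely elsewhere: the early-intervention programme for young children is described as for ages 1 to 6 in Background, while Study setting gives below 6 for a trial with the same citation. That makes a slip plausible, but it does not close the gap. The limit below 6 appears in both text and table and cannot be read as including age 6.

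**The study is exploratory.** The analysis section says that the study will likely be underpowered and that quantitative results are preliminary. This lowers the priority but does not remove the point, since scores never collected cannot be recovered.

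A second gap might be inferred for self-rated pain and itch, where the text has "children 8 years or older to rate pain and itch intensity" and the table's default is "young person aged over 8 years (unless otherwise indicated". That is a clerical mismatch: caregiver ratings still cover eight-year-olds.

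**Conclusion.** The point holds, at moderate severity. As written, eligible children aged 6.0 to under 7.0 years have no listed instrument for a primary outcome, and the age-stratified analysis carries the gap forward.

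The size cannot be fixed from the documents. About 10 of 180 children without a baseline distress score is the result under uniform ages, and 4 to 18 is the range if 2% to 10% of the sample are aged 6. These counts also assume that 180 children are recruited; with another total, they scale in proportion. The consequence is reduced coverage and some loss of precision for distress. The effect on adjusted models for other outcomes is conditional on where the traumatic stress covariate comes from and on whether it is adjusted for.

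**What to change.** 1. Make the two age bands meet, in the text and in footnotes a and b of Table 2. Assign six-year-olds to whichever of the two instruments is supported at that age. The documents do not show which one that is, so the sponsor needs to check the instruments' own age ranges.
2. State that age at baseline decides the instrument, and keep the same instrument through the 3- and 6-month visits, so that each follow-up score has a baseline on the same scale. The same check should cover children who turn 6 or 7 during follow-up.
3. If neither instrument is supported at age 6, say that six-year-olds are outside the distress analysis, and report the distress denominator accordingly.
4. If data collection is already complete, report what six-year-olds were actually given and show the distress denominator by age.

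The cost is a change of wording and of the survey's branching rule. No extra visits or staff are needed, and the anticipated total of 180 does not change.

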### Primary health professional outcomes

Change in knowledge scores and self-efficacy will be measured using questions designed for the study and recorded as part of the online package (see Additional File 1 and 2).

Secondary and healthcare resource outcomes to be collected at baseline and 3-months post-baseline in the control and intervention period are as follows:
Administered pain relief: the number (percentage) of patients administered first and second line medications will be recorded. The dose of pain relief and other medication for symptom management will also be recorded.Rate and adjunct interventions (e.g. music therapy, counselling) for pain relief or reduction of stress symptoms.Number of psychosocial or mental health referrals: this will be recorded from medical records.Patient attendance rates at booked appointments and patient reminders: the percentage of booked appointments attended will be measured as well as the number of patient reminders sent by text, mail or phone as per standard practice.Time to wound healing: this will be measured using the time taken in days from the burn injury to ≥ 95% of the wound area re-epithelialized with no further wound dressings required. Re-epithelialization will be assessed by experienced burn consultant or specialised burn nursing staff.

In addition, hospitalisation-related resource use and costs will be collected from hospital administrative records for 12-months prior to the control period for each patient and for the 6-months after the intervention period for each patient for informing cost-related modelling for use in future economic evaluations of web-based education platforms.

Sociodemographic and clinical data will be collected from the following:

(1) The Queensland Paediatric Burns Registry or medical records (maintained by the Centre for Children’s Burns and Trauma Research) including percent total body surface area (TBSA), percent full thickness burn, length of time post-burn, spontaneous skin healing versus grafted site, type of burn and length of time to re-epithelialisation.

(2) Patient and/or caregiver self-report using a standard sociodemographics and clinical data form and questionnaires collecting data on household education, employment, income and occupation, scar location, skin type, age, gender and comorbidities

(3) Fidelity of the intervention based on the commencement and completion rate

(4) Intervention details: time taken to complete the intervention, number of times accessed and number of staff who complete the package per discipline

These other outcomes will be used to describe the control and intervention groups and use of the intervention, as well as to be entered into analyses as predictors or confounding factors to be controlled for.

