The acceptability of the Responsive CARE intervention to health professionalsThe demand for trauma-informed care training and use (or intended use) of the Responsive CARE intervention by health professionals in a tertiary, outpatient burn clinical settingTo what extent the Responsive CARE intervention training can be delivered using existing resources and infrastructure within the tertiary, clinical settingBarriers and enablers in the implementation environment and feasibility of the recruitment pathway to inform the amount and type of resources at different organizational levels (e.g. clinician, supervisor, manager) required to implement the intervention successfully

Specific objectives for the investigation of patient-centred outcomes are to:
Determine preliminary evidence of effectiveness of the intervention on a health professional’s knowledge, attitude and behaviours. This will provide preliminary indication of the extent to which skills and knowledge following the completion of the intervention have been applied and an evaluation of factors that drive clinician behaviour change.Determine preliminary evidence of effectiveness of the intervention on child’s acute pain, itch, distress (i.e. traumatic stress reactions), caregiver’s treatment satisfaction and health-related quality of life. This will provide an indication of whether the intervention can show change within this group. It is hypothesised that child participants will experience less acute pain, itch and distress in the posttest compared to the pretest period, and caregiver participants will experience enhanced treatment satisfaction in the posttest compared to the pretest, following staff completion of the responsive CARE intervention.Estimate healthcare resource use and costs of delivering the intervention to inform cost-related modelling for use in future economic evaluations of web-based education platforms.

The TIDierR checklist [35] and CONSORT-EHEALTH checklist (V.1.6.1) [36] have been used to detail the intervention and evaluation and CONSORT extension to pilot and feasibility trials [37] for reporting the study protocol.

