## Method

### Study design

The feasibility study will employ a pretest posttest observational design using mixed methods to evaluate acceptability, demand, implementation and practicality [34] of the Responsive CARE intervention. Using a mixed methods approach will allow for the collection of quantitative data in terms of the demand for the intervention as well as rich qualitative data to understand the factors affecting implementation that may ultimately impact on the intervention’s sustainability and/or scalability. Purposive sampling will be used for the qualitative study components. Interviews will cover five main areas: understanding of trauma-informed care practice, experience of trauma-informed care, clinician’s readiness to change, acceptability of the Responsive CARE intervention and identify potential barriers and enablers to implementing an e-learning package within organizational culture.

A mixed method, pretest posttest comparison design will be used to examine preliminary effectiveness, with consecutive sampling of children and caregivers. Baseline quantitative data will be collected during a 3-month control period followed by a 3-month intervention period. Follow-up of participants will be completed at 3 months and 6 months after baseline for participants in the control and intervention periods. Between the control and intervention periods, there will be a 1-month period to implement the e-learning intervention. Qualitative interview data will also be collected from caregivers in the control and intervention periods, who will be purposively sampled.

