4. Taking CARE of yourself	This module explores the challenges that may arise for health professionals working with children and families who experience medical traumatic stress. Checklists to increase self-awareness of signs of stress in this setting, as well as evidence-based strategies to manage their own well-being are provided.

The Responsive CARE intervention will be freely available to all health professionals working in burn outpatients via ilearn.health.qld.gov.au from the commencement of the 1-month training period (June 2019) and until the 6-month follow-up intervention period is completed (April 2020). Technical assistance is available via web-based or hotline numbers provided on the ilearn site. No changes will be instigated to the content of the Responsive CARE intervention throughout the intervention period (including 6-month follow-up). No automated prompting will be provided to the user once enrolled. New health professionals to the burns centre during the intervention period and 6-month follow-up will be informed of the study and undergo training of how to access the site following informed consent with clinician researcher (MS) or research assistant as close to commencing in the recruiting centre as possible. It is anticipated that open access to the responsive CARE intervention will be available from ilearn.health.qld.gov.au at the completion of data collection. Testor accounts are currently available upon request to the author (MS). Alternatively, an overview of the content is provided in Additional File 3.

A logic model has been developed (see Fig. 2) to demonstrate the predicted outcomes and impact of the intervention.

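### The administrative cost windows are anchored to the study periods instead of each child's baseline; read literally, they skip the seven months holding every baseline visit and cover the two cohorts unequally

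*Protocol article*

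**What the plan says.** The cost rule is in the Outcomes section of the protocol article, under Primary health professional outcomes. Hospitalisation-related resource use and costs are drawn from hospital administrative records "for 12-months prior to the control period for each patient and for the 6-months after the intervention period for each patient". The purpose is given in the objectives at the end of the Background: "Estimate healthcare resource use and costs of delivering the intervention to inform cost-related modelling for use in future economic evaluations of web-based education platforms".

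The timetable is in Study design: "Baseline quantitative data will be collected during a 3-month control period followed by a 3-month intervention period". Also: "Between the control and intervention periods, there will be a 1-month period to implement the e-learning intervention". Clinical follow-up runs on a different clock from the cost windows: "Follow-up of participants will be completed at 3 months and 6 months after baseline for participants in the control and intervention periods".

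Two calendar dates appear in the section on the Responsive CARE intervention. The training month is June 2019, and the 6-month follow-up of the intervention period ends in April 2020.

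The Outcomes section also lists itemised resource data: "Secondary and healthcare resource outcomes to be collected at baseline and 3-months post-baseline in the control and intervention period are as follows". The items include medication, adjunct interventions, psychosocial referrals, attendance and reminders. Table 2 places EuroQol-5D-Y and CHU-9D at baseline, 3 months and 6 months.

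**The concern.** The children form two consecutive cohorts, and a control child has no intervention period of their own. A window that opens before the control period and another that opens after the intervention period therefore sit at different distances from baseline in the two cohorts. Neither window includes the months in which the children are enrolled.

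Resource use and cost is a stated objective, repeated in the Conclusion, and its value lies in feeding later economic models. Those models need costs over a defined interval after baseline, the same for every child, and paired with utilities over that interval. EuroQol-5D-Y and CHU-9D are on each child's own clock, and the cost windows as worded are not. A modeller would have utilities for months 0 to 6 and hospital costs for a different span, which depends on cohort and enrolment date.

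**Working it through.** **Inputs.** Control period 3 months, training 1 month, intervention period 3 months, and follow-up to 6 months after each child's baseline (Study design). Training in June 2019 and end of follow-up in April 2020 (Responsive CARE intervention section). Cost windows of 12 and 6 months (Outcomes).

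**Assumptions.** Periods start on the first of the month. For the averages only, baseline dates are uniform within each 3-month period.

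**Step 1: reproduce the plan's calendar.** 1 June 2019 + 1 month training + 3 months intervention + 6 months follow-up = 1 April 2020. This matches the stated April 2020, so the inferred calendar is sound. Control is March to May 2019 and intervention is July to September 2019.

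**Step 2: place the windows.** Let month 0 be the start of the control period. Control is 0 to 3, training 3 to 4 and intervention 4 to 7.
- Pre window: −12 to 0, i.e. March 2018 to February 2019.
- Post window: 7 to 13, i.e. October 2019 to March 2020.
- Uncovered: 0 to 7, i.e. 3 + 1 + 3 = 7 months, March to September 2019. All baselines lie here.

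**Step 3: position relative to baseline b.** The post window opens 7 − b months after baseline and closes 13 − b months after. The pre window ends b months before baseline.

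| | Control (b = 0 to 3) | Intervention (b = 4 to 7) |
|---|---|---|
| Post window opens, months after baseline | 4 to 7 | 0 to 3 |
| Post window closes, months after baseline | 10 to 13 | 6 to 9 |
| Pre window ends, months before baseline | 0 to 3 | 4 to 7 |

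The offset between cohorts is 3 + 1 = 4 months throughout.

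**Step 4: share of follow-up captured.** The overlap of (b, b + w) with the post window is max(0, b + w − 7) months. The pre window adds nothing, because b is never below 0.
- Control, w = 3: b + 3 is at most 6, so 0 months are captured for every child.
- Control, w = 6: overlap is max(0, b − 1), range 0 to 2. The mean is (1/3) × ∫ from 1 to 3 of (b − 1) db = (1/3) × 2 = 0.67 months; 0.67/6 = 11%.
- Intervention, w = 3: overlap is b − 4, range 0 to 3, mean 1.5 months; 1.5/3 = 50%.
- Intervention, w = 6: overlap is b − 1, range 3 to 6, mean 4.5 months; 4.5/6 = 75%.

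**Step 5: the same check with a per-child window.** A window from b to b + 6 captures 6 of 6 months in both cohorts, with no gap and no offset.

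**The case against.** The best defence is that the sentence means something other than its literal text. It says twice that the windows are per patient, which adds little if they are fixed calendar blocks. Elsewhere (Procedures, and the Responsive CARE intervention section) the article uses intervention-period language for follow-up counted to 6 months after baseline. If the post window means each child's own 6-month follow-up, the gap and the offset largely disappear. This stands as a plausible intention. It does not rescue the wording, which names the control period for one window and the intervention period for the other, and nothing else in the article supplies an administrative cost window for March to September 2019.

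Several stronger readings are tempting but unsupported:
- *A cost difference between cohorts would be biased.* The article plans no such comparison. The purpose is modelling input, costs are not named in the analysis paragraphs, and quantitative outcomes are to be treated as preliminary.
- *Resource use during treatment is not recorded at all.* Itemised data are collected at baseline and 3 months in both cohorts. The gap concerns hospitalisation-related use and costs from administrative records.
- *A per-child reading would not help, because it contrasts time without a burn with time after one.* No within-child before-after contrast is planned, and Step 5 shows that a per-child window restores full coverage.
- *The look-back predates the injury for nearly all children.* The sample projection uses new referrals, but eligibility also admits children attending for scar management, and days post-burn at baseline is listed as a potential confounder. Some will have had earlier burn care.
- *Windows of 12 and 6 months are an error in themselves.* A longer look-back is harmless when the two are not contrasted.

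**Conclusion.** The point holds as a fault in the stated rule, with a limited consequence. Followed as written, the rule misses the seven months containing every baseline visit. It captures none of the control cohort's first 3 months after baseline, and about 11% of that cohort's first 6 months against about 75% for the intervention cohort. The cost inputs would be incomplete, unequal between cohorts and not aligned with the utilities.

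The seven-month gap and four-month offset follow from the stated period lengths alone. The 11% and 75% also assume uniform recruitment; without that assumption, individual coverage of the first 6 months ranges from 0 to 2 months for control and 3 to 6 months for intervention. All these figures rest on the literal reading. No hypothesis test is affected. The change is worth making because the objective depends on these data and the correction is cheap.

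**What to change.** Reword the cost sentence so that both windows run on each child's own clock, identically in the two cohorts:

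1. Hospital resource use and cost from the child's baseline to 6 months after baseline. This matches the span of the EuroQol-5D-Y and CHU-9D assessments.
2. The 12 months before the child's baseline, kept only as a descriptor or covariate.
3. Cost from injury to baseline reported separately. That interval varies with days post-burn, so adding it to item 1 would again mix follow-up cost with time since injury.
4. Training delivery cost reported separately from hospital cost.

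The cost is a change of dates in the administrative data request, with no patient contact. For items 1 and 2 the outer dates do not move. The earliest baseline (March 2019) less 12 months is March 2018, and the latest (end of September 2019) plus 6 months is the end of March 2020. The request becomes one continuous 12 + 7 + 6 = 25-month extract. Item 3 may need to reach further back for children with older burns.
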